### Procedure

Following random selection and allocation of the 12 tertiary hospitals, eligible female inpatients with breast cancer from each hospital will receive either MSNP plus routine nursing care immediately after recruitment (intervention arm), or only routine nursing care (control arm). The patients in both arms will provide demographic data and complete the pre-test of the FACT-Bv4.0, VAS, arm circumference, and CMS prior to the intervention. After the baseline measurement, four post-tests (i.e., FACT-Bv4.0, VAS, arm circumference, and CMS) at 1, 3, 6, and 12 months will be conducted. Items on the questionnaire will be asked of all patients and their answers will be recorded by trained data collectors. The flow chart of the cRCT procedure is depicted in Fig. 2.

**Fig. 2 Fig2:**
[figure not shown]
Flowchart of the trial. (FACT-Bv4.0: Functional Assessment of Cancer Therapy-Breast version 4.0; VAS: visual analogue scale; CMS: Constant-Murley Score; MSNP: multimodal standard nursing program.)

### Outcomes and measurements

The primary outcome is HRQoL measured by the Functional Assessment of Cancer Therapy-Breast version 4.0 (FACT-Bv4.0) at 12 months.

#### FACT-Bv4.0

The 36-item Chinese (simple) FACT-Bv4.0 consists of a general cancer subscale (FACT-G) and a breast-cancer-specific subscale for additional concerns (BCS). The FACT-G comprises physical well-being (PWB, seven items), social/family well-being (SFWB, seven items), emotional well-being (EWB, six items), and functional well-being (FWB, seven items). The BCS comprises nine items, each rated on a 5-point Likert scale (from 0 to 4). The FACT-Bv4.0 total score, which is the sum of scores of the FACT-G and BCS ranges from 0 to 144. A higher score indicates better HRQoL of the patient [52]. The reliability, validity, and responsiveness of the Chinese (simple) FACT-Bv4.0 has been confirmed in Chinese patients with breast cancer [53].

The secondary outcomes include pain, fatigue, sleep, BCRL, and upper limb function evaluated by a visual analogue scale (VAS), the circumference method, and the Constant-Murley Score (CMS) at 1, 3, 6, and 12 months.

#### VAS

The VAS is a psychometric response scale used to measure subjective characteristics or attitudes that cannot be directly assessed. When answering a VAS item, respondents specify their level of agreement with a statement by indicating a position along a continuous line between two end-points [54]. In this study, a 0–10 cm VAS will be used in the subjective evaluation of pain (no pain to severe pain), fatigue (no fatigue to severe fatigue) and sleep (good sleep to poor sleep) in the patients.

#### Circumference method

Arm circumference will be measured at 10 cm above the wrist and 10 cm above the elbow using a leather measuring tape. Lymphedema is defined as a difference in arm circumference of more than 2 cm between the treated and untreated side at either of the two measured locations on the limb [55]. The measurement of arm circumference of all recruited patients will be consistently performed at 5 pm at the baseline survey and at each post-test.

#### CMS

The Chinese CMS has four subscales, including pain (15 points maximum), activities of daily living (20 points maximum), range of motion (ROM, 40 points maximum), and strength (25 points maximum). The total score ranges from 0 to 100, with a higher score indicating a higher quality of functioning [56]. A systematic review showed that the original CMS satisfied psychometric properties of functional assessment [57].

### Interventions

#### The intervention arm

Patients in the intervention arm will receive the MSNP based on routine nursing care delivered by trained clinical nurses immediately after recruitment. The MSNP includes physical care, help with psychological adjustment, and social support, aiming to improve the physical, psychological, and social functioning of the patients, respectively. Detailed information on the MSNP content and implementation are shown in Table 1.

**Table 1 Tab1:** Outline of the multimodal standard nursing program (MSNP)

Section	Target	Content	Implementation	Special attention
Physical care	Physical function	Systematic functional exercises		
		• Upper limb exercise (two-sides)	Exercises of the finger, wrist, forearm, elbow, upper arm, shoulder, head & neck; 5–10 times per day, 15 min per session.	Patients with complications and abnormal conditions should limit the time and strength of exercise. Continue to the end of follow-up.
		• Aerobic exercise	Walking up and down stairs, 3–6 times per day, 30 min per session.	
		• Progressive muscle relaxation	Sitting or lying, relaxing from head to feet, 3–6 times per day, 30 min per session.	
Psychological adjustment	Psychological function	Psychological counseling	Nurse-conducted one-to-one communication on the patient’s psychological problems; twice per week, 30–60 min per session in the hospital. Need-oriented counseling is delivered via outpatient review or telephone after discharge from the hospital.	Continue to the end of follow-up.
		Music listening	Listening to patient’s preferred light music via MP3 player; twice per day (7 a.m.–9 a.m. and 9 p.m.–11 p.m.), 30 min per session.	Patients with sound allergy or who dislike listening to music should not be given such intervention. Continue to the end of follow-up.
		Interactive distraction	Need-oriented communication with caregivers or peers while in a negative mood.	Continue to the end of follow-up.
Social support	Social family function	Family support training	Training caregivers on the monitoring of the patient’s diet, exercise, rest and illness, as well as coping with the negative influences of breast cancer on families. Once per week, 60 min per session in the hospital. Need-oriented training is delivered via outpatient review after discharge from the hospital.	Continue to the end of follow-up.
		Peer group support	Rehabilitation experiences exchange between the patient and peers, discussing successful recovery in a chatty manner. Once per week, 60 min per session in hospital setting. Need-oriented support is delivered via outpatient review after discharge from the hospital.	Continue to the end of follow-up.

#### The control arm

Patients in the control arm will only receive routine nursing care, including vital signs observation, nursing specific to surgery, drainage tube nursing, fundamental exercises after surgery, and post-operative complications monitoring.

### Masking

All recruited female patients with breast cancer, participating clinical staff, and trained data collectors of the 12 hospitals will be blinded to the allocation information. Patients in the control arm will not be offered any information on the MSNP during the study period in case of bias.

The trial statistician will also be blinded to the treatment code during development of the statistical analysis plan and writing of the statistical programs, which will be validated and completed using dummy randomization codes. The actual allocation will only be provided to the study team after locking of the database.

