## Methods

### Design

This is a two-arm single-blind cluster randomized controlled trial (cRCT) in clinical settings with female breast cancer patients.

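### The Masking section says clinical staff and the study team are blind, which the trial's own procedures rule out; the single-blind label does not match the groups listed, so protection of a subjective primary outcome is overstated.

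*Protocol article*

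**What the plan says.** The Design section states: "This is a two-arm single-blind cluster randomized controlled trial (cRCT) in clinical settings with female breast cancer patients". It does not say which party is blind.

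The Masking section, echoed in the Methods part of the Abstract, covers all recruited patients and adds that "participating clinical staff, and trained data collectors of the 12 hospitals will be blinded to the allocation information". Its second paragraph adds two more parties. For the statistician: "The trial statistician will also be blinded to the treatment code during development of the statistical analysis plan". For the study team: "The actual allocation will only be provided to the study team after locking of the database". The only concrete measure given for patients is that control patients are told nothing about the multimodal standard nursing program (MSNP).

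On delivery, the section on the intervention arm says that patients "receive the MSNP based on routine nursing care delivered by trained clinical nurses immediately after recruitment". The Abstract gives the duration as 12 months. The control arm has routine nursing care only. Under Sample size and randomization, whole hospitals are allocated, six per arm, by a member of the research team.

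On measurement, the Procedure section says: "Items on the questionnaire will be asked of all patients and their answers will be recorded by trained data collectors". The primary outcome is the FACT-B total score at 12 months.

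**The concern.** A masking statement tells readers how far to trust an outcome that depends on what patients say and how their answers are taken down. Here it names parties who must know the arm in order to do their work. FACT-B is a self-report instrument, and in this trial the answers pass through an interviewer. If patients or interviewers expect a benefit, part of any difference between arms may reflect reporting rather than quality of life. A larger sample does not remove such a difference. The findings are to be reported under the CONSORT guidelines for cluster trials, so a masking claim that the design contradicts would carry into the results paper and be read as protection that the trial did not have.

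**Working it through.** This point rests on comparing the article's statements, party by party.

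1. **Nurses at intervention hospitals.** Masking says that participating clinical staff are blind and makes no exception. The intervention section has trained clinical nurses deliver the MSNP. Table 1 includes one-to-one counselling, caregiver training and peer groups, and the comparator has no sham or attention component. A nurse trained in these components who delivers them knows that her hospital provides them. Each hospital is wholly in one arm, so she knows the arm of every patient there. The two statements cannot both stand.

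2. **Study team.** Masking withholds the allocation from the team until database lock. Sample size and randomization has a team member carry out the allocation, so at least that person knows it from the start. Someone must also arrange training at the six intervention hospitals. The article does not say who, but if that person belongs to the team, the statement fails for them too.

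3. **Patients.** Intervention patients know that they receive the programme. They need not know that it is the experimental condition. Control patients, told nothing of it, may be unaware that an alternative exists. Patient blindness is therefore at most partial: unawareness of the other arm.

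4. **Data collectors.** They are stated to be blind. Nothing in the article makes this impossible, but they question patients who can reveal their care.

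5. **Statistician.** Blind while the analysis plan and programs are written, with dummy codes. This is feasible and is not disputed.

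6. **Label.** Single-blind suggests one blinded party. Masking lists patients, clinical staff, data collectors, the statistician and the study team.

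**Scale, for illustration only.** No stated figure depends on masking. The planned size reproduces without it: design effect 1 + (30 − 1) × 0.1 = 3.9; 90 × 3.9 = 351; 351 / 30 = 11.7, rounded up to 12 hospitals, or 360 patients.

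The article gives no SD. Assuming a two-sided 5 % test with 80 % power, 37 per arm and a difference of 6.74 imply SD = 6.74 / [(1.960 + 0.842) × √(2/37)] ≈ 10.35. With 6 × 30 = 180 patients per arm, SE = 10.35 × √(2 × 3.9 / 180) ≈ 2.15 points.

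Suppose there were no true effect and a pure reporting bias b. The two-sided false-positive rate is then 1 − Φ(1.96 − b/SE) + Φ(−1.96 − b/SE), or its noncentral t analogue on 10 df:

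| Assumed bias b | Points | Share of 6.74 | Normal | t, 10 df |
|---|---|---|---|---|
| 0.1 SD | 1.03 | 15 % | 7.7 % | 7.2 % |
| 0.2 SD | 2.07 | 31 % | 16.1 % | 14.0 % |
| 0.3 SD | 3.10 | 46 % | 30.2 % | 25.7 % |

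The values of b are assumptions. The table shows how sensitive the test would be to a bias. It does not show that one exists.

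**The case against.** The strongest reply is that a behavioural programme with a patient-reported outcome cannot be fully masked by anyone, that the remaining risk survives any rewording, and that no analysis or sample size changes. That is true. It limits the point to what the trial may claim, but it does not make the claim correct. It can also be said that the sentence on the study team closes the paragraph on the statistician and may mean only that the treatment code is released for analysis after lock. That narrower meaning is plausible, but the text does not say so.

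Several stronger inferences are tempting, and the article does not support them:

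- **That data collectors cannot be blind.** The phrase linking them to the 12 hospitals closes a list. It does not say who employs them or that each works at one site, and operational safeguards may be in the full protocol.
- **That patient blinding fails outright.** In a cluster design, control patients can be unaware of the alternative. Written consent does not show otherwise, because its content is not given.
- **That the VAS is described inconsistently.** The VAS section says that "respondents specify their level of agreement with a statement by indicating a position along a continuous line". This is a general description of the scale, and a collector can present the line and record the position indicated. The Procedure section does not say that VAS lines are read aloud.
- **That signing the analysis plan before unmasking gives no protection.** The statistician's blindness and the dummy codes are real safeguards, and nothing in the article shows that they fail.

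**Conclusion.** The point holds with high confidence for three matters: the blinding of clinical staff is contradicted by the intervention section; blindness of the study team until lock is contradicted at least for the member who allocates the hospitals; and the design label does not match the list of blinded groups. For patients, the claim is too broad rather than wholly wrong. For data collectors and the statistician, masking is achievable and may stand as stated.

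The consequence is that protection against expectation and interviewer bias in an interviewer-recorded, subjective primary outcome is overstated. A reader might go on to infer that the result will be biased by some number of points. The documents give no basis for that: the bias is a risk of unknown size, and the illustration rests on an implied SD and assumed biases. No planned number needs to change.

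**What to change.** Rewrite Masking, and align the Abstract and the design label with it, to say that:

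- nurses delivering care are not blind;
- members of the study team who allocate the hospitals or train the nurses are not blind;
- patients are at most unaware of the alternative arm;
- the masked parties are the data collectors, who are not told the hospital's arm, and the statistician.

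Do not report the trial as blinded for clinical staff. This costs only wording and a less favourable masking statement.

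Two inexpensive additions are worth making. First, let patients who can read complete FACT-B themselves on the existing paper forms, in both arms alike. This reduces interviewer influence, though not patient expectation, and may leave slightly more missing items. Second, have collectors record their guess of the allocation, so that the report can show how far their masking held. This adds one item to the form.

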### Data management and analyses

SAS 9.4 and SPSS 22.0 will be employed to perform all statistical analyses. All quantitative data will be collected using paper questionnaires with unique ID numbers for each recruited patient. Data will be stored at the research team office at the end of each day. Daily checking of data will be carried out by the research coordinator, with queries identified and resolved promptly. A database will be built using Epidata3.1; double entry and checking will be performed by an assigned data entry team. Discrepancies will be resolved by a third data manager. Once in an electronic file, all data will be password protected, with data managers controlling access to passwords and ensuring the database is backed up daily.

Findings of the trial will be reported according to the CONSORT guidelines for cRCT. Primary analyses will be based on an intention-to-treat (ITT) population and secondary analyses on a per-protocol (PP) population. The primary endpoint will be analyzed using a linear mixed model with intervention, time, and interaction between intervention and time as fixed effects, baseline measurement as covariate, and cluster and patient as random effects. The intervention difference at each time, together with its 95 % confidence interval will be derived from the mixed model. Missing data will be treated as missing at random in the above mixed model analysis and no imputation will be made. To assess the sensitivity of the result of this assumption, the last observation carried forward (LOCF) strategy will be used to compute missing HRQoL scores during follow-up. A covariate-adjusted mixed model of the primary endpoint will be tested by adding pre-specified covariates at baseline into the linear mixed model. Subgroup analysis will be performed on the pre-specified covariates.

Continuous secondary outcomes will be analyzed in a similar way to the primary endpoint analysis. For the analysis of binary secondary outcomes, a generalized mixed model will be employed with intervention, time, and the interaction between intervention and time as fixed effects, baseline measurement as covariate, and cluster and patient as random effects. The odds ratio (OR) between the two arms at each time, together with its 95 % CI will be derived from the generalized mixed model.

All analyses will be described in detail in the finalized and signed statistical analysis plan before unmasking the study.

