## Abstract

**Background:**

Breast cancer and its treatment-related adverse effects are harmful to physical, psychological, and social functioning, leading to health-related quality of life (HRQoL) impairment in patients. Many programs have been used with this population for HRQoL improvement; however, few studies have considered the physical, psychological, and social health domains comprehensively, and few have constructed multimodal standard nursing interventions based on specific theories. The purpose of this trial is to examine the effect of a health belief model (HBM)-based multimodal standard nursing program (MSNP) on HRQoL in female patients with breast cancer.

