### Participants

Participants are inpatients with breast cancer. Inclusion criteria are newly diagnosed with breast cancer, female, aged 18 years and older, preparing to receive radical mastectomy and other auxiliary treatments (e.g., chemotherapy, radiotherapy, endocrine therapy), and providing written informed consent. Patients with cognitive disorders, psychiatric disorders, other malignant tumors, active infection, or other severe potential infection will be excluded. Cognitive disorders and psychiatric disorders will be screened using DSM-V (Diagnostic and Statistical Manual of Mental Disorders, 5^th^ ed.) criteria [49]. Reasons for refusal to participate will be documented.

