### Sample size and randomization

The sample size was calculated based on the FACT-Bv4.0 total score of similar intervention studies (two-arm trials with Chinese mainland female patients with breast cancer employing a 12-month follow-up period). According to an eligible study [50], 74 patients (37 in each arm) will be needed to detect a between-arm change of 6.74 in the FACT-Bv4.0 total score with a power of 80 % at a 5 % level of statistical significance. The sample size was increased to 90 patients (45 in each arm) to allow for a 20 % dropout rate. Assuming an intra-cluster correlation coefficient (ICC) of about 0.1 and 30 patients per cluster, the sample size adjusting for clustering is 12 clusters or 360 patients [51]. That is, a total of 12 tertiary hospitals will be required in the trial, with 6 hospitals in each arm and 30 patients per hospital on average.

The 12 tertiary hospitals will be randomly selected from the 24 tertiary hospitals in Xi’an district and allocated to the intervention and control arms using a computer-generated random numbers table. Selection and allocation of the 12 hospitals will be carried out independently by a member of the research team.

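### LOCF is the only missing-data sensitivity analysis the article names, and it is a poor check of missing at random for a 12-month quality-of-life endpoint

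*Protocol article*

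**What the plan says.** Under Data management and analyses, the protocol article sets the assumption for the primary linear mixed model: "Missing data will be treated as missing at random in the above mixed model analysis and no imputation will be made". The next sentence sets out to examine how sensitive the result is to that assumption, and names the method: "the last observation carried forward (LOCF) strategy will be used to compute missing HRQoL scores during follow-up". The same section also plans per-protocol, covariate-adjusted and subgroup analyses. None of these changes the missing-data assumption. Details are deferred to a signed statistical analysis plan, which is not shown.

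Four other places bear on whether LOCF suits that purpose:

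- Outcomes and measurements fixes the endpoint: "The primary outcome is HRQoL measured by the Functional Assessment of Cancer Therapy-Breast version 4.0 (FACT-Bv4.0) at 12 months".
- Procedure sets the visits whose scores could be carried forward: "four post-tests (i.e., FACT-Bv4.0, VAS, arm circumference, and CMS) at 1, 3, 6, and 12 months will be conducted".
- Participants places entry before surgery: "preparing to receive radical mastectomy and other auxiliary treatments (e.g., chemotherapy, radiotherapy, endocrine therapy".
- The abstract's Background links treatment to impaired quality of life: "Breast cancer and its treatment-related adverse effects are harmful to physical, psychological, and social functioning, leading to health-related quality of life (HRQoL) impairment".

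Sample size and randomization gives the dropout allowance: "The sample size was increased to 90 patients (45 in each arm) to allow for a 20 % dropout rate".

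**The concern.** The article does not leave this detail open. It names a method and gives it a purpose, and the method serves that purpose badly. The risk to a missing-at-random analysis is that patients who leave have unseen 12-month scores different from those of comparable patients who stay. A useful check moves that difference through a range and shows when the conclusion gives way. LOCF fixes it at one value per patient, and that value depends on how scores happen to move between the last visit and month 12. The trialists do not choose it.

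No change after the last visit is implausible here. Patients enter before surgery, adjuvant treatment follows, and the primary model itself carries time and intervention-by-time terms.

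Dropout could also differ between arms. Table 1, at face value, asks intervention patients for 75–150 minutes of limb exercise, 90–180 of aerobic exercise, 90–180 of relaxation and 60 of music a day. That is 315–570 minutes, with exemptions for some patients, while controls receive routine care only. If the arms lose patients at different rates or times, LOCF can move the estimate either way for reasons unrelated to missing at random.

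**Working it through.** **Plan's own figures.** 37 × 1.2 = 44.4, rounded up to 45 per arm, or 90 in all. The design effect is 1 + (30 − 1) × 0.1 = 3.9. Then 90 × 3.9 = 351, and 351/30 = 11.7, so 12 hospitals and 360 patients. The stated size reproduces and is not in question. At 20 % dropout, 0.2 × 360 = 72 patients lack a 12-month score, leaving 24 of 30 per hospital.

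**Formula.** The expected LOCF mean in an arm is the sum, over last-observed visits, of the proportion leaving there times the mean at that visit, plus the completers' proportion times the 12-month mean.

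**Illustration A (assumed).** Control means relative to month 12 are −10, −8, −4 and 0 at 1, 3, 6 and 12 months. Effects are 2, 4, 5.5 and 6.74. Dropout is completely at random, with last visits equally at 1, 3 and 6 months. Carried-forward means are (−10 − 8 − 4)/3 = −7.33 for control and (−8 − 4 + 1.5)/3 = −3.5 for intervention.

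- 20 %/20 %: 0.8 × 6.74 + 0.2 × (−3.5) − 0.2 × (−7.33) = 6.16.
- 25 % intervention/15 % control: 0.75 × 6.74 − 0.875 + 1.10 = 5.28, which is 22 % below 6.74.
- 15 %/25 %: 0.85 × 6.74 − 0.525 + 1.83 = 7.04.
- No true effect, 10-point imbalance in dropout: 0.10 × 7.33 = ±0.73.

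**Illustration B (assumed).** Control means are 100, 92, 90, 95 and 100 at baseline, 1, 3, 6 and 12 months. Last visits are spread equally over baseline, 1, 3 and 6 months, so the control carried-forward mean is 94.25, or 5.75 below month 12. Dropout is given as intervention/control.

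| Assumed effect at baseline, 1, 3, 6, 12 months | True at 12 | LOCF 20/20 | LOCF 10/30 | LOCF 30/10 |
|---|---|---|---|---|
| 0, 1, 2.5, 4.5, 6.74 | 6.74 | 5.79 | 7.42 | 4.17 |
| 0, then 6.74 throughout | 6.74 | 6.40 | 7.72 | 5.08 |
| none | 0 | 0 | 1.15 | −1.15 |
| 0, 6.74, 6.74, 4, 0 | 0 | 0.87 | 1.59 | 0.16 |

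**What LOCF assumes about dropouts.** In row 1, intervention dropouts are set at 94.25 + 2.0 = 96.25 against 106.74 for completers, a shift of −10.49. Controls are shifted by −5.75. The net shift is −4.74, and 0.2 × (−4.74) = −0.95, which gives 5.79. In row 2 the net shift is −7.435 + 5.75 = −1.69. In row 4 it is −1.38 + 5.75 = +4.37, in favour of the intervention. Both size and sign therefore follow from the trajectory.

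**What LOCF leaves unvaried.** Keep row 1 and 20 % missing per arm. Let the unseen intervention-arm 12-month mean lie *s* points below its missing-at-random value. The true difference is 6.74 − 0.2*s*, that is 6.74, 5.74, 4.74, 2.74 and 0 for *s* = 0, 5, 10, 20 and 33.7. Throughout, the missing-at-random estimate stays at 6.74 and LOCF at 5.79. No analysis can estimate *s* from the observed data; a delta analysis differs in showing the result at each value.

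**How far a delta range must reach.** No SD is given. Back-solving 37 per arm (two-sided 5 %, 80 % power) gives 6.74/(√(2/37) × 2.80) ≈ 10.35, with about 10.2 as the lower end. With 6 hospitals per arm and 24 completers each, and no gain from baseline adjustment, SE = √(2 × 10.35² × (0.1 + 0.9/24)/6) ≈ 2.2. With t = 2.228 on 10 df, an observed 6.74 has a lower 95 % limit of about 6.74 − 4.94 = 1.8. At 20 % missing, a shift of −6.74 in the intervention arm moves the estimate by 1.35, which is not enough. The tipping shift is about −1.8/0.2 = −9. An equal shift in both arms cancels under equal dropout (0.2δ − 0.2δ = 0).

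**Standard error.** Counting 30 rather than 24 scores per hospital as observed multiplies the SE by √(0.1300/0.1375) ≈ 0.97, about 3 % too small.

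**The case against.** The best defence is that LOCF is itself one departure from missing at random. In Illustration A it places intervention dropouts 10.2 points below completers (−3.5 against 6.74) and control dropouts 7.3 below (−7.33 against 0). A reader might infer from the criticism that LOCF never allows for dropouts doing worse; these numbers show that it can. What remains is that the size and direction of the departure are not controlled.

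A reader might also infer that LOCF is the only robustness check of the primary result. It is not, since per-protocol and covariate-adjusted analyses are planned. It is the only missing-data sensitivity analysis named in this article, and the unseen analysis plan may add others.

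The movements are modest against an SE of about 2.2. Equal dropout in Illustration A moves LOCF by 0.58 (about a quarter of an SE), the null imbalance by 0.73 (a third) and the 25 %/15 % split by 1.46 (two-thirds). The SE understatement is small too. All this stands, and it limits the weight of the point.

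Finally, the article gives no dates for chemotherapy or radiotherapy, and endocrine therapy could still be running at month 12. Calling the carried-forward scores treatment-phase scores is therefore an inference. It is well supported by the entry criteria and visit schedule, but it is not stated.

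**Conclusion.** The point holds as a weakness in the choice of sensitivity analysis and should be corrected. The article assigns LOCF to examine missing at random. LOCF answers with one no-change assumption that does not fit this population and follow-up, so neither agreement nor disagreement with the mixed model says much about departures from missing at random.

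It would be wrong to read this as bias in the primary result: LOCF does not enter the primary estimate, and under the dropout completely at random assumed in Illustration A the mixed model is unbiased. The harm is a misleading statement about robustness, in either direction. The range of about 4.2 to 7.7 around a true 6.74 and the null shifts of up to ±1.15 rest on assumed trajectories, dropout timing and dropout splits of up to 30 %/10 %. The tipping shift near −9 rests on a back-solved SD, an ICC of 0.1, 20 % missing and an observed difference equal to the design value.

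**What to change.** In Data management and analyses, and in the analysis plan, replace LOCF as the check of missing at random with the following:

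- Multiple imputation of missing FACT-B scores that respects hospital clustering, with delta shifts added to the imputed 12-month scores.
- Shifts applied to the intervention arm alone, and with different values by arm. Equal shifts in both arms show little when dropout is equal.
- A range that continues until the 12-month conclusion changes, beyond −6.74 if needed, with that tipping point reported so that clinical readers can judge its plausibility.
- A control-based imputation for intervention-arm dropouts.

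LOCF may be dropped, or kept as a supportive analysis that is not described as the test of missing at random. The cost is a change of wording and some extra programming, with no new data. Because the article has the analysis plan finalised before unmasking, the change can be made blind.
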